## Abstract

**Introduction:**

Transient ischaemic attack (TIA) and minor stroke are frequently assumed as temporary or non-disabling events. However, evidence suggests that these patients can experience relevant impairment and functional disability. Therefore, the present study aims to evaluate the feasibility and effectiveness of a 3-month multidomain intervention programme, composed of five non-pharmacological strategies, aimed at accelerating return to pre-event level of functionality in patients with TIA or minor stroke.

**Methods and analysis:**

Patients diagnosed with a TIA or a minor stroke are being recruited at the emergency or neurology departments of the Hospital Pedro Hispano, located in Matosinhos, Portugal (n=70). Those who accept to participate will be randomly allocated to two groups (1:1): (a) Intervention—receives a 3 months combined approach, initiating early post-event, composed of cognitive training, physical exercise, nutrition, psychoeducation and assessment/correction of hearing loss; (b) Control—participants will not be subject to any intervention. Both groups will receive the usual standard of care provided to these diseases. Recruitment began in May 2022 and is expected to continue until March 2023. Socio-demographic characteristics, lifestyles, health status, cognitive function, symptoms of anxiety and depression and quality of life will be assessed; as well as anthropometry, blood pressure and physical condition. Time to complete or partial recovery of instrumental activities of daily living will be assessed using an adapted version of the Frenchay Activities Index. All participants will be evaluated before the intervention and after 3 months.

**Ethics and dissemination:**

This study was approved by the Ethics Committee of the Local Health Unit of Matosinhos (Ref. 75/CES/JAS). Written informed consent will be required from all the participants; data protection and confidentiality will be also ensured. The findings of this project are expected to be submitted for publication in scientific articles, and the main results will be presented at relevant scientific meetings.

**Trial registration number:**

NCT05369637.

Strengths and limitations of this studyThis protocol describes a pilot randomised controlled trial addressing the effect of an innovative multidomain non-pharmacological intervention programme on post-transient ischaemic attack and minor stroke functionality.The intervention programme will start early after the diagnosis of the vascular event, maximising health gain and targeting brain plasticity.The main outcome is based on the time to recover instrumental activities of daily living after the event, which is more suitable due to the characteristics of residual impairment.This study will explore a wide range of different outcomes, including study feasibility, cognitive function, lifestyle behaviours, physical and emotional status.Given the characteristics of the intervention, blinding of the participants is not possible. In addition, the main outcome is evaluated by self-report and is based on a predefined list of activities of daily living. Therefore, we cannot exclude the existence of recall bias regarding our main outcome.

## Introduction

A transient ischaemic attack (TIA) is defined as a ‘transient episode of neurological dysfunction caused by focal brain, spinal cord, or retinal ischemia, without acute infarction’ by the American Heart Association,^1^ while a minor stroke is suggested to occur when a patient has a score of ≤3 in the National Institutes of Health Stroke Scale (NIHSS).^2^ Population-based studies have shown that the age-adjusted incidence of TIA in the European population ranges from 28 to 59/100 000/year^3^ and, in Portugal, a higher annual TIA incidence of 74/100 00/people was estimated between 2009 and 2011.^4^ This is particularly relevant since previous studies have described an increased risk of stroke after these events,^5^ and, in 2019, stroke was the third leading cause of disability-adjusted life years.^6^

The study of the overall morbidity associated with a TIA or a minor stroke is often neglected, since most of the time they are assumed as being transient or non-disabling events. However, evidence suggests that these patients can experience relevant disability even with a NIHSS of 0 or 1.^7^ A decreased performance in activities of daily living (ADLs) up to 1-year post-event was also observed, including in patients without any apparent physical disability.^8 9^ Other studies showed a high prevalence of depression and apathy,^10^ cognitive impairment,^11^ physical deficits^12^ and hearing degeneration,^13^ with implications on patients’ return to work, social relations and activities.^14^ Moreover, European guidelines on management of TIA recommend for early initiation of secondary prevention following such an event,^15^ focusing particularly on the leading risk factors for stroke, namely high systolic blood pressure, body mass index, fasting plasma glucose and smoking.^6^

Taken together, these findings highlight the importance of multidomain interventions aiming to promote functioning levels among patients with TIA or minor stroke, and to develop preventive actions and health promotion plans specifically designed for this group. As such, this pilot study primarily aims to explore the feasibility and the effectiveness of an innovative multidomain intervention programme, composed of five strategies: cognitive training, physical exercise, nutrition education, psychoeducation and assessment/correction of hearing problems. These are aimed at accelerating the return to pre-event functionality in patients with a TIA or a minor stroke diagnosis. The primary objectives are as follows:

To assess the feasibility of methodology for early recruitment, collecting information and delivering the interventions.To estimate the effectiveness of this programme on the time to recovery in each instrumental ADLs.

As secondary objectives, the effect of this intervention on cognitive function, adherence to the Mediterranean diet, physical function, basic ADLs, symptoms of anxiety and depression, quality of life, anthropometric measures and blood pressure, will be also assessed.

## Methods and analysis

### Study design

The present study is a two-arm parallel, superiority, pilot randomised controlled trial (RCT), which will be nested in the ongoing project ‘Multiple Interventions to Prevent Cognitive Decline’ (MIND-Matosinhos).^16^ This proposed pilot study will provide crucial information about the logistic feasibility, provide estimates of eligibility, recruitment and attrition rates, optimising the study design. It will also enable a greater precision in the power and sample size calculations of a future full-scale study.

The primary endpoints will be the feasibility of this multidomain programme, as well as the time to recovery to pre-event functionality after the occurrence of a TIA or a minor stroke. A block randomisation with a 1:1 allocation will be performed.

### Setting

This pilot RCT will be conducted at the department of neurology of the Hospital Pedro Hispano E.P.E (HPH), as part of the Local Health Unit of Matosinhos (ULSM), which is integrated in the Portuguese National Health Service. The HPH is located at the Matosinhos municipality, Northern Portugal, and is responsible for providing care to 318 000 inhabitants from the municipalities of Matosinhos, Vila do Conde and Póvoa de Varzim.

### Eligibility criteria

Patients aged 18–85 years old and with a clinical diagnosis of TIA or minor stroke as defined by an NIHSS score ≤3 are eligible for this study. Additional inclusion criteria include: the onset of symptoms within the last 7 days; first-time stroke or TIA; at least 4 or more years of education; discharged home without the need for inpatient rehabilitation; modified Rankin Scale (mRS) 0–2. Patients will be excluded if they are unable to attend the face-to-face intervention sessions, or if they have: previous diagnosis of dementia or severe disability; contraindication for physical exercise, severe loss of hearing, vision or communication skills; frailty, reduced life expectancy due to severe disease or need for regular treatments that compete with availability for intervention (eg, chemotherapy, haemodialysis).

### Recruitment

Participants will be enrolled through consecutive sampling from the Neurology Department (stroke or emergency care units) of HPH. Healthcare professionals from the recruitment site will be informed about the protocol and their potential role, and an experienced researcher will be on-site to provide coordination. The neurology medical team will be responsible for screening eligibility and obtaining written informed consent for all the participants. Recruitment started on 11 May 2022.

### Randomisation

The participants will be randomly assigned (1:1) to the intervention or control group after the baseline assessment. Randomisation will be done using a computer-generated programme, using random blocks of four sizes. A researcher who is not immediately engaged in the project will implement the randomisation process.

### Data collection

Participants will be evaluated at baseline (before the beginning of the intervention programme) and at 3 months, as depicted in figure 1. Data on socio-demographic (birth date, sex, address, marital status, education, occupation, income), medical history, current medication, lifestyle (smoking and alcohol use, physical activity and sedentary behaviours) and adherence to Mediterranean diet^17^ will be collected through structured questionnaires applied by a trained researcher. Anxiety and depression,^18^ memory problems^19^ and quality of life^20^ will be evaluated through self-administered questionnaires validated for the Portuguese population. Additionally, long-term cognition data will be also collected every 3 months for a period of up to 10 years using Brain on Track (BoT), a web-based tool for remote longitudinal assessment of different cognitive domains.^21^ The outcome measure section describes the instruments in detail.

**Figure 1 F1:**
[figure not shown]
Study design flowchart

Data regarding clinical diagnosis, onset of symptoms, hospital admission and discharge date, mRS score, NIHSS score, medical history of cerebrovascular events, age and need for inpatient/outpatient rehabilitation will be retrieved from the patient′s medical record. Clinical characteristics of the cerebrovascular event will also be collected.

### Intervention

The intervention will be implemented over 3 months and will comprise five different components, including cognitive training, physical exercise, nutritional education, psychoeducation and assessment and correction of hearing problems. Only the intervention group will be exposed to all or any of the components of this comprehensive intervention programme. Both groups will continue to receive the usual standard of care provided to this type of clinical disease in the hospital setting. The usual standard of care consists of the initiation of the appropriate secondary prevention and referral to the outpatient cerebrovascular diseases clinic (telephone call at 1-month post-event and in-person appointment at 3 months post-event). Depending on the clinical presentation and neurological deficits, patients can also be referred to an outpatient physical medicine and rehabilitation appointment.

Since early intervention post-vascular event is decisive, given the time interval between neurological injury and the onset of nervous function recovery activities, intervention sessions are aimed to begin within no later than 15 days after the cerebrovascular event. Considering this timeline, once the participants are recruited and randomised, the intervention will start immediately, especially cognitive training.

To minimise refusals and losses to follow-up, all evaluations and sessions will be scheduled by the participant’s preference. A written plan with the intervention schedules will be given and sessions reminded through email or phone messages in the day before (day, time and location). If one intervention session is missed, efforts will be placed to arrange another suitable time in another group and individualised meetings will be rescheduled. If not possible, the missed appointment will be documented, and the dropout or non-compliance reasons will be registered for further analysis.

#### Cognitive training

Monthly in-person sessions in groups of a minimum of five participants (60 min) will be conducted by a psychologist. Additionally, during the 3 months a daily home-based cognitive training individual (30 min) sessions using the COGWEB^22^ online platform will be performed. This online computer tool provides cognitive training tailored to each patient’s deficits with different difficulty levels, allowing continuous treatment monitoring, clinical evolution and adherence compliance.^22^ Exercises are aimed at different cognitive domains, such as attention, memory, executive function, language and calculus.^22^ Participants have access to instructions for each exercise before initiating the session, displayed on the screen and through the speakers. Instructions can be seen at any moment, even throughout the session. Participants without access to a computer will receive paper/pencil equivalent home-based cognitive exercises.

#### Physical exercise

Physical exercise sessions in-person or remotely twice a week with a duration of up to 60 min, guided and supervised by a graduated physical exercise technician, will be conducted. Activities will be tailored to each participant tolerance, medical history and comorbidities, focusing on impaired balance and weakness. During exercise sessions, the exercise technician will track symptoms of chest pain, shortness of breath, wheezing, dyspnoea, lightheadedness, nausea, among others. Small groups allow to set short and attainable goals with the participants and have a graded exercise programme, starting with reduced intensity and gradually increasing.

In-person sessions will be preferred, however if online sessions are needed, the participants without a computer will receive booklets with physical exercise instructions twice a week and the researcher will contact the participants to assess adherence to the exercises.

#### Nutritional education

Intervention arm will include individual appointments (three appointments with a nutritionist, once a month with a duration of 45 min to 60 min) and in-person group cooking sessions (once a month with a duration of 90 min). During individual sessions, the nutritionist will emphasise the benefits of adhering to the Mediterranean diet and salt reduction, particularly for overall cardiovascular health advantages. Group sessions start with the nutritionist’s presentation of healthy recipes and further analysis of nutritional values, then the participants will undergo its preparation. In these sessions, participants can bring their partners or one family member.

#### Psychoeducation

Monthly in-person psychoeducation sessions (60 min) in groups of a minimum of five participants will be conducted by a psychologist. These sessions will support people in understanding, exploring, and self-managing their emotions and impairments, through peer support and promotion of lifestyle changes.

#### Assessment and correction of hearing problems

At the beginning of the intervention programme, a hearing assessment and correction will be performed. This evaluation will be conducted by otolaryngologists and audiologists, who will evaluate previous hearing problems and use of hearing aids, and includes otoscopy and audiogram. Those detected with any hearing problem will be referred for a medical appointment with an otolaryngologist.

### Primary outcome measures

The primary outcomes for the study are related with its feasibility and time to partial or complete recovery of each instrumental ADLs.

To evaluate the feasibility of this study, the following primary outcomes will be assessed:

Recruitment time frame: proportion of participants recruited within 7 days after onset of symptoms. It will be assessed by dividing the number of participants recruited within the time frame divided by the total number of participants.Beginning of the intervention: proportion of participants that started any of the interventions no later than 15 days after onset of symptoms.Adherence to each component of the intervention: proportion of adherence to each component of the intervention and different intervention modalities (remote/in person), calculated as the number of sessions attended divided by the total number of sessions provided. For the COGWEB training, the outcome will be the absolute number of sessions.Dropout: proportion of participants who dropped out of the study, calculated as the number of participants who dropped out after attending at least one session divided by the total number of participants who attended at least one session.

Time to recovery in each instrumental activity of daily living will be measured by an adapted version of the Frenchay Activities Index (FAI). The translated and validated version of the FAI—adapted version for the Portuguese population^23^ will be used to assess the instrumental ADLs functional performance at baseline and follow-up at 3 months. The version used in this study is based on the perception of the patient’s capacity to perform a specific instrumental ADLs instead of its frequency, as stated in the original scale developed by Holbrook and Skilbeck.^24^ The scale consists of 15 activities, scored from 1 to 4 (1-could not do at all; 2-very difficult; 3-a little difficult; 4-not difficult at all).^23^ Although the original index suggests that total scores for men and women should be considered separately,^24^ in the present study the score of each activity will be analysed independently, as the interest in exploring the impact of the programme in each activity.

For the present study, only activities that are part of participants’ daily lives will be considered, namely those that were performed at least once in the last 12 months. Time to recovery will be defined as the time from the start of the intervention programme to the time of complete or partial recovery. Each participant will report their level of performance in each activity at the baseline and follow-up at 3 months. In the baseline, if a participant scores a specific activity as altered (score 1–3), their level of performance before the TIA or minor stroke will be confirmed to understand if the change in the activity performance is related with the cerebrovascular event. It will be also inquired and recorded the date when a difficulty in a certain activity ceased. The average of activities altered post-event (score 1, 2, 3) at baseline and the average of activities that improved in both groups on completing the intervention programme will be measured.

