### Data analysis and sample size

The associations between the social and clinical characteristics and feasibility (eg, recruitment time frame, adherence, dropouts) and lifestyle outcomes will be quantified through linear or logistic regression models, as applicable. Time in days from the onset of symptoms to complete or partial recovery in each instrumental ADLs will be estimated and illustrated by Kaplan-Meier survival curves. The time comparison between intervention and control groups will be made through the log-rank test. To estimate the association between the intervention and the recovery time, HRs will be estimated, through the computation of univariate and multivariate Cox regression models.

Training of the interviewers and use of standardised procedures for data collection is expected to contribute to a low proportion of missing data, and no imputation is being planned.

To the best of our knowledge, there is no previous information regarding effect sizes and SDs regarding the primary outcome related with the recovery of functionality after a TIA or a minor stroke. Nevertheless, a sample size of at least 70 participants (35 per arm) is commonly recommended for a pilot study when estimating the pooled SD.^25^ Nevertheless, taking into account the results of a previous RCT evaluating a cardiac model of rehabilitation for reducing risk factors post-TIA and stroke,^26^ this sample size will allow to detect mean differences of 5.5 and 6.0 in the changes observed in the Hospital Anxiety and Depression Scale—anxiety and depression scores, respectively, between intervention and control groups (assuming a statistical power of 80% and a level of significance of 5%).

To achieve the sample size needed to accomplish the proposed objectives, we expect to invite approximately 100 individuals, since a participation of 70% was previously observed in the EPIPorto cohort.^27^ We also expect a dropout of 10% from baseline to the first follow-up; nevertheless, and in order to minimise refusals and losses to follow-up, all activities will take place near participants’ residence and be scheduled for their convenience.

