### Contingency plan

This study intents to recruit participants within 7 days after the onset of symptoms and start intervention no later than 15 days, which is a considerably short period. This recruitment time frame may be difficult to attain, so additional measures may have to be adopted, namely receive referrals from other hospitals in neighbouring counties (eg, Porto).

Due to the COVID-19, the number of in-person sessions and participants per group may be reduced. However, if necessary, all activities will be home-based. To minimise the potential impact of the pandemic on participation and retention rates, additional mitigation measures may be adopted, including enlarging the recruitment period or an increase in the sample size.

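### If the 7-day inclusion criterion is applied at recruitment, the primary endpoint for early recruitment is about 100% by construction and measures compliance with the criterion, not feasibility

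*Protocol article*

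**What the plan says.** All references are to the protocol article.

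- **Introduction.** The first primary objective is "To assess the feasibility of methodology for early recruitment, collecting information and delivering the interventions".
- **Eligibility criteria.** The inclusion criteria contain "the onset of symptoms within the last 7 days; first-time stroke or TIA". The date from which the 7 days are counted back is not named.
- **Recruitment.** "Participants will be enrolled through consecutive sampling from the Neurology Department". The neurology team screens for eligibility and takes consent.
- **Primary outcome measures.** The first feasibility outcome is the "proportion of participants recruited within 7 days after onset of symptoms", obtained by "dividing the number of participants recruited within the time frame divided by the total number of participants".
- **Data analysis and sample size.** Linear or logistic regression, as applicable, is planned to relate social and clinical characteristics to "feasibility (eg, recruitment time frame, adherence, dropouts" and lifestyle outcomes. The sample size is 70, from about 100 people invited at 70% participation.
- **Contingency plan.** The 7-day aim is described as an intention, with the remark "This recruitment time frame may be difficult to attain". The measures offered are referrals from other hospitals and, because of COVID-19, a longer recruitment period or a larger sample.
- **Study design.** The pilot is to yield eligibility, recruitment and attrition rates for a future full-scale trial.

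**The concern.** The condition that admits a patient is the same condition that the endpoint counts. A patient first identified on day 8 is the failure that a measure of early recruitment should detect. Under the stated rules that patient is ineligible, does not become a participant, and so leaves no trace in the proportion.

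Early recruitment is part of the first primary objective, and the authors themselves doubt that the window can be met. A near-perfect figure could be read as evidence that the window works, when it shows only that the inclusion rule was followed. The planners of the full-scale trial would need the opposite information: how many otherwise suitable patients the window costs.

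**Working it through.** **Is there a figure to reproduce?** The article gives no expected value, target or precision for this endpoint. The only related figure is the recruitment forecast, which reproduces: 100 invited × 0.70 = 70 participants.

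**Step 1. Who is in the denominator?** The article uses "participants" for people who have been screened, have consented and are enrolled (Abstract, Recruitment). For the roughly 100 people to be invited it uses a different word. No section defines the denominator as patients screened, identified or invited.

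**Step 2. Can a patient enrol after day 7?** No section allows it. The contingency measures widen the source of patients, the recruitment period or the sample. None relaxes the criterion.

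**Step 3. The endpoint under the stated rules.** Let N = 70 be the participants and d the number enrolled late in breach of the criterion.

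Endpoint = (N − d)/N

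| d | Endpoint | Exact 95% CI |
|---|---|---|
| 0 | 70/70 = 100% | 94.9% to 100% |
| 1 | 69/70 = 98.6% | 92.3% to 99.96% |
| 3 | 67/70 = 95.7% | 88.0% to 99.1% |
| 5 | 65/70 = 92.9% | 84.1% to 97.6% |

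For d = 0 the lower limit is 0.025^(1/70) = 0.949. That interval has no real sampling meaning here, because the value is fixed by the inclusion rule. The number of patients missed because of the window appears nowhere in the formula.

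**Step 4. The regression.** With d = 0 the yes/no outcome equals 1 for everyone, so a logistic model has no variation to fit. With d between 1 and 5 there are at most five events of the rarer kind, and each is a protocol deviation.

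**Step 5. What an informative denominator would show.** Let M be all identified patients who meet every criterion other than the 7-day one. The article does not give M, so the values below are assumptions, with 70 recruited in time.

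| M (assumed) | 70/M | Exact 95% CI |
|---|---|---|
| 80 | 87.5% | 78.2% to 93.8% |
| 100 | 70.0% | 60.0% to 78.8% |
| 140 | 50.0% | 41.4% to 58.6% |

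The endpoint as defined is 100% in all three rows.

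**Step 6. Lateness and refusal must be kept apart.** A ratio of consenting patients to all otherwise eligible patients mixes the two. With the article's own 100 invited and 70 consenting, and nobody late, 70/100 = 70% arises from refusal alone. With M = 140 (assumed) and 100 approached in time, timely approach is 100/140 = 71.4%, consent is 70/100 = 70%, and the product is 50%. Only the 71.4% describes the window.

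**The case against.** The strongest reply is that the endpoint is ambiguous and has not been shown to be constant. A reader might infer that it must equal exactly 100% in every circumstance. The article does not support that, for three reasons.

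- Eligibility deviations lower it.
- Neither the reference date of the criterion nor the date of recruitment is defined. Randomisation follows a baseline assessment, so a patient eligible at screening on day 6 could be counted as recruited on day 8.
- The Contingency plan uses the language of an aim, so the window may have been meant as a target.

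All of this stands, and it is why the point is conditional on the criterion being applied at recruitment. It does not rescue the endpoint. No section permits late enrolment, and patients screened out as late are absent from the denominator on any of these datings.

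A reader might also infer that the pilot will yield no useful recruitment information. That goes too far. Study design promises eligibility and recruitment rates, screening is consecutive, and onset and admission dates are taken from the medical record. The outcome on starting the intervention by day 15 is not fixed by eligibility in this way. What remains is that no outcome under Primary outcome measures or in Table 1 isolates patients lost to the window.

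Finally, a reader might infer that the planned regression is impossible in any form. It is not. Days from onset to recruitment vary within the window and could be modelled linearly. The difficulty is confined to the yes/no outcome, which is the one the article defines.

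**Conclusion.** The point holds in conditional form. If onset within 7 days is enforced at recruitment, the first primary feasibility outcome is about 100% apart from eligibility deviations: 100% with none and 92.9% with five among 70. It then measures compliance with an inclusion criterion and cannot inform the objective on early recruitment. Its yes/no form cannot support the planned logistic regression.

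This rests on two readings: that "participants" means enrolled people, and that no enrolment is allowed after day 7. Both follow from the article's usage, but neither is spelled out.

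The reach is limited. This is one of four primary feasibility measures, and no target or progression threshold is attached to it. The between-group comparison of recovery time, the sample size and the randomisation are untouched. How many patients the window excludes is unknown, and the 50% to 87.5% range above is illustration only.

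**What to change.** 1. Reconcile Eligibility criteria, Primary outcome measures and Contingency plan. State whether 7 days is a criterion or a target, and which date counts as recruitment.
2. Redefine the denominator as all consecutively identified patients with TIA or minor stroke who meet every inclusion and exclusion criterion other than the 7-day window.
3. Report separately (a) the proportion of these identified and approached within 7 days, (b) the proportion of those approached who consented, and (c) the reasons for non-enrolment. Give exact confidence intervals for the proportions.
4. Add the median and interquartile range of days from onset to identification and from onset to consent.
5. Fit the regression for this outcome on the screened set, as far as the variables are available for patients who were not enrolled, or on days to recruitment among those enrolled.

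The cost is rewording and a short screening log with onset date, identification date and reason not enrolled. Consecutive screening is already planned, and onset and admission dates are already to be retrieved for participants. Intervention and randomisation are unaffected. The downside is a reported proportion that will probably look less favourable than the present one.
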